### 2.6. Sample Size Considerations

The sample size was calculated by a priori analysis in G * Power, version 3.1.9.7 (The G*Power Team, Düsseldorf, Germany).

Because the design of this project has never been employed in children and adolescents with MLD, we could refer only to a pilot study that determined the effects of tRNS, combined with cognitive training, in children with MLD [66]. However, the study included 12 children with a medium effect size but differs in several aspects from ours: the number of tRNS sessions, number of groups, and cognitive training. To be conservative and start from these premises, we calculated the expected effect size (f) to low and estimated it at 0.15.

With an estimated f = 0.15, α value = 0.05 (i.e., probability of false positives of 5%), and β = 0.80 (i.e., at least 80% power), the sample size that was required for repeated-measures analysis of variance (RM ANOVA) with 3 groups (Frontal Group vs. Parietal Group vs. Sham Group) and 4 measurements (T0 vs. T1 vs. T2 vs. T3) was 78 (i.e., 26 per group). Considering a 30% dropout rate in the follow-ups, we will plan to recruit a total of 102 participants (i.e., 34 per group).

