### 3.2. Statistical Analysis

The Shapiro–Wilk test will be used to test the normality of the data, and Levene’s test will be performed to analyze the homogeneity of the variances. When the data are normally distributed and the assumption of homogeneity is not violated, parametric analyses will be computed. When one assumption is not met, nonparametric tests will be conducted or log-transformation of the distribution will be applied, if appropriate. When appropriate, sphericity will be verified by Mauchly’s sphericity test. When sphericity is not met, Greenhouse–Geisser correction will be applied.

Chi-square analysis will be used to compare groups with regard to demographics, blindness, and safety measures (categorical variables).

Linear mixed-effects models, which account for within-subject correlations more optimally than analysis of variance and automatically handle missing values, allowing maximum use of available data [93], will be run to compare groups for primary (continuous variables: number line subtest) and secondary outcomes (continuous variables: arithmetic, neuropsychological, and psychological measures). The R package lme4 v1.1–17 [94,95], which estimates model parameters using restricted maximum likelihood estimation and computed *p*-values per Satterthwaite’s method [96], will be used. The linear mixed-effects models will include Group (Frontal, Parietal, and Sham) and Time (T0, T1, T2, T3) as fixed factors and Participants as the random factor. Baseline performance will be included as a covariate in our model, because it allows us to make better adjustments for minor differences in pretreatment means. The same analysis will be performed for the training accuracy data, including Group (Frontal, Parietal, and Sham) and Day (from 1 to 10) as fixed factors and participants as the random factor.

Pearson’s correlation will be used to determine whether and the extent to which arithmetic improvements are related to changes in neuropsychological measures, psychological measures, and spectral power of EEG frequency bands at T1, T2, and T3 (from T0).

The statistical results will be corrected for multiple comparisons by Bonferroni’s correction where appropriate.

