### 3.3. Hypothesis and Expected Results

We expect to observe the following:(1)The Parietal, Frontal, and Sham groups will not differ in blindness or safety measures;(2)The Parietal and Frontal groups will experience significant improvements in the primary outcome (Number Line subtest accuracy) and arithmetic and neuropsychological measures at T1 compared with Sham group and that such improvements will persist at T3. The Parietal and Frontal groups will also significantly improve their training accuracy across the 10 days versus the Sham group. We do not have a directional hypothesis on the differences between the 2 active groups (Parietal and Frontal);(3)The Parietal and Frontal groups will significantly improve their psychological measures at least at T3 compared with the Sham group;(4)In the Parietal and Frontal Groups, arithmetic changes will correlate strongly and positively with changes in neuropsychological and spectral power EEG measures at least at T1 and with changes in psychological measures at least at T3.

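### Single-step Bonferroni is valid, but Holm's step-down procedure gives the same error control and more power for the prediction that both active groups beat Sham

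*Protocol article*

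**What the plan says.** Section 3.2 of the Protocol article closes with its only statement on multiplicity: "The statistical results will be corrected for multiple comparisons by Bonferroni’s correction where appropriate". It names no family and no number of tests.

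Section 3.3 lists what the investigators expect: "The Parietal and Frontal groups will experience significant improvements in the primary outcome (Number Line subtest accuracy"), compared with Sham at T1 and lasting to T3. It gives no direction for Frontal against Parietal, although electrode placement is one of the objectives in section 1.3. A family at one visit could therefore hold two contrasts (each active arm against Sham) or three.

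Section 2.6 sizes the trial on an overall repeated-measures test with "3 groups (Frontal Group vs. Parietal Group vs. Sham Group) and 4 measurements (T0 vs. T1 vs. T2 vs. T3"), using "α value = 0.05 (i.e., probability of false positives of 5"%). The required number "was 78 (i.e., 26 per group"), raised to 102 (34 per group) for dropout. No power is given for any pairwise contrast.

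**The concern.** Bonferroni compares every p-value in a family of m tests with α/m. Holm compares the smallest with α/m, the next with α/(m − 1), and so on, and stops at the first failure. The guarantee on family-wise error is the same and needs no assumption about how the tests are correlated.

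The difference shows when several contrasts are expected to be positive together, and section 3.3 predicts exactly that: both active arms better than Sham. What is at stake is the chance of confirming that joint prediction in a trial of 26 evaluable participants per arm. False-positive control is not at stake.

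**Working it through.** **1. The plan's own figure.** Inputs from section 2.6: f = 0.15, α = 0.05, power 80%, k = 3 groups, m = 4 visits. Assumed, because not stated: correlation ρ = 0.5 between visits, sphericity, and the group-by-time interaction as the test.

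- λ = f²·N·m/(1 − ρ) = 0.0225 × 78 × 4 / 0.5 = 14.04
- df1 = (3 − 1)(4 − 1) = 6; df2 = (78 − 3)(4 − 1) = 225
- Power = 0.801, and 78 is the smallest N that reaches 0.80.

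The stated 78 is reproduced. The multiplicity correction does not enter this calculation, so changing it leaves N as it is.

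**2. Direction of the difference.** Holm's thresholds α/m, α/(m − 1), …, α are never below α/m. If a p-value is at most α/m, every smaller one is too, so Holm rejects them all. The first step is identical, so the chance of at least one rejection in the family is identical. In simulation (400,000 runs), Holm rejected everything that Bonferroni did in every run. Under the global null, the family-wise error was 4.6% for both methods with two contrasts and 4.4% for both with three.

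**3. An effect consistent with f = 0.15.** Assume that both active arms gain the same d (in SD units) at T1, T2 and T3, and that Sham gains nothing. The interaction variance is d² × (2/3 × 1/3) × (3/4 × 1/4) = d²/24. Hence d = 0.15 × √24 = 0.735.

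**4. Contrast at T1, adjusted for baseline.** With ρ = 0.5 the residual variance is 1 − 0.25 = 0.75 SD².

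- 26 per arm: SE = √(2 × 0.75/26) = 0.240; d/SE = 3.06
- 34 per arm: SE = √(2 × 0.75/34) = 0.210; d/SE = 3.50

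Tests are taken as two-sided at a family level of 0.05. With two contrasts, Bonferroni needs both p-values at or below 0.025. Holm needs the smaller at or below 0.025 and the larger at or below 0.05.

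**5. Power for both active arms to beat Sham at T1**

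| Family | n per arm | Bonferroni | Holm | Gain (points) |
|---|---|---|---|---|
| 2 contrasts | 26 | 66.0% | 75.8% | 9.8 |
| 3 contrasts | 26 | 59.4% | 65.9% | 6.5 |
| 2 contrasts | 34 | 81.4% | 88.1% | 6.7 |
| 3 contrasts | 34 | 76.4% | 81.5% | 5.1 |

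Power for at least one active arm to beat Sham at 26 per arm is the same under both methods: 89.7% with two contrasts and 86.2% with three.

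**6. Sensitivity (26 per arm, two contrasts, both arms beat Sham)**

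| Assumption | Bonferroni | Holm |
|---|---|---|
| d = 0.3 | 6.2% | 10.1% |
| d = 0.5 | 26.3% | 35.9% |
| d = 0.735, change scores not adjusted for baseline | 48.9% | 60.0% |
| d = 0.735, averaged over T1 to T3 | 93.5% | 96.5% |

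The gain runs from about 3 to 11 points, and its sign does not change.

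**The case against.** The strongest reply is that nothing in the plan is wrong. Bonferroni is a standard method, it does not inflate type I error, it contradicts no other section, and no stated figure depends on it. All of that stands.

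A reader might infer more: that the plan locks in a large loss of power across all arms and visits. The article does not support that. It corrects only where appropriate, states no family, and lists expectations instead of a rule that every contrast must be significant. It does not say that persistence to T3 will be shown by separate significance tests. Larger families of arms by visits would show bigger differences, but those families would be the reader's own construction.

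If success did require both arms to beat Sham, that pair would need no adjustment. Testing each at 0.05 gives 76.7% at 26 per arm, so Holm would not be the main remedy. This also stands. But the article does not define success that way, and it treats placement as a question in its own right, so separate claims for each arm are plausible. For those, Holm at 75.8% recovers almost all of the unadjusted power and keeps family-wise control.

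Finally, Bonferroni tests agree with simple simultaneous intervals and Holm tests do not. That is a legitimate reason to prefer Bonferroni, though the article does not give it.

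**Conclusion.** The point holds as a matter of efficiency. Wherever the plan would apply Bonferroni, Holm gives the same family-wise guarantee and never rejects less; this needs no assumption about effect, correlation or family. The family-wise error guarantee and the planned N of 78 do not change. Nor, with equal gains in the two active arms, does power for at least one of them to beat Sham.

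For both arms to beat Sham at T1, the gain is about 10 points (two contrasts) or 6.5 points (three) at 26 per arm, and about 7 or 5 points at 34 per arm. These sizes rest on a within-person correlation of 0.5, equal gains in the two active arms, baseline adjustment, and d = 0.735 as the reading of f = 0.15. None of the first three values, nor the family, can be taken from the sample size section, so the figures are illustrations. It would be wrong to conclude that the trial's error control or its sample size calculation fails because of the Bonferroni choice.

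**What to change.** Before unblinding, replace Bonferroni's correction in section 3.2 with Holm's step-down procedure, for every family in which Bonferroni would have been applied. This changes one phrase in the text and one setting in the software. It needs no more participants and no new data.

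The cost lies in reporting. Holm has no simple matching simultaneous intervals, so a contrast significant by Holm may carry a Bonferroni- or Dunnett-adjusted interval that includes zero. The report should say which intervals are shown. If agreement between tests and intervals matters more to the investigators than the extra power, keeping Bonferroni is defensible, and the plan should give that reason.

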### 3.3. Hypothesis and Expected Results

We expect to observe the following:(1)The Parietal, Frontal, and Sham groups will not differ in blindness or safety measures;(2)The Parietal and Frontal groups will experience significant improvements in the primary outcome (Number Line subtest accuracy) and arithmetic and neuropsychological measures at T1 compared with Sham group and that such improvements will persist at T3. The Parietal and Frontal groups will also significantly improve their training accuracy across the 10 days versus the Sham group. We do not have a directional hypothesis on the differences between the 2 active groups (Parietal and Frontal);(3)The Parietal and Frontal groups will significantly improve their psychological measures at least at T3 compared with the Sham group;(4)In the Parietal and Frontal Groups, arithmetic changes will correlate strongly and positively with changes in neuropsychological and spectral power EEG measures at least at T1 and with changes in psychological measures at least at T3.

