### 1.3. Research Objectives

The overarching goal is to provide a scientific foundation for devising brain-directed and evidence-based treatments in children and adolescents with MLD. Based on insights from recent empirical research, this study addresses at least five gaps in research:(1)Examining the long-term safety and feasibility of a multisession tRNS protocol in the pediatric population (e.g., 10 sessions);(2)Determining the effects of the tRNS setup (over bilateral dlPFCs vs. bilateral PPCs) in improving long-lasting arithmetic learning and performance and neuropsychological and psychological measures compared with sham tRNS;(3)Testing whether and the extent to which arithmetic improvements after tRNS are related to neuropsychological changes;(4)Understanding whether and the extent to which changes in spontaneous EEG after tRNS are linked to arithmetic improvements;(5)Assessing whether and the extent to which improvements in arithmetic performance correlate with changes in the psychological function of children and their parents’ stress.

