## 4. Discussion

We have described the rationale and design of a trial that aims to determine whether tRNS, combined with cognitive training, will have a clinically meaningful impact on math and math-related (e.g., working memory, mental rotation) abilities and psychological and neurophysiological measures in children and adolescents with MLD. This study will constitute the first attempt to prove the safety and feasibility of multiple (e.g., 10 sessions) and consecutive sessions of tRNS in the pediatric population. In addition, the project will determine the most effective placement of tRNS electrodes (Frontal vs. Parietal) compared with placebo (Sham) in terms of behavioral and neurophysiological long-term improvement. The results will represent a significant step toward clinical translation in the field.

A unique facet of this study relies on the potential synergy of multitarget interventions, with one each serving as “endogenous” activation, targeting behavior through cognitive training, and “exogenous” neuromodulation [55] through its direct neurophysiological effect on brain regions that surround the electrodes on distal cortical areas. Accordingly, tRNS would act to desynchronize pathological cortical rhythms via enhancing the neural signals detection and thus improving the neural processing and the related behavior [58,60,97]. In our case, tRNS has the potential to prompt math training-induced neuroplasticity, facilitating brain activity in the frontal or parietal network during cognitive training.

An additional unique feature is that our study will involve repeated consecutive sessions of tRNS combined with cognitive training as multiple sessions of transcranial electrical stimulation gave higher chances of cumulative biological effects over time [98]. The decision of a multi-sessions protocol was made after cautiously considering neurophysiological and preliminary data that supported evidence for tolerability and safety of this technique in children at this stage [66,99,100]. In line with our considerations, a recent study [73] applied five-days of tRNS combined with cognitive training in children with attention deficit hyperactivity disorder and the authors revealed no clinical-meaningful side effects or related safety-issues at any follow-up.

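### The safety aim is paired with a no-difference hypothesis and a chi-square difference test, which cannot support a safety conclusion for uncommon side effects; estimation should replace it

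*Protocol article*

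**What the plan says.** All places are in the protocol article.

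- Section 1.3 puts safety first among the research gaps: "Examining the long-term safety and feasibility of a multisession tRNS protocol in the pediatric population (e.g., 10 sessions".
- Section 2.5.6 has children grade symptoms on four levels, from absent to severe, after each session and at T1, T2 and T3.
- Section 2.6 sizes the trial for the repeated-measures efficacy analysis only, with 26 per group evaluable and 34 per group recruited. It gives no safety power and no expected side-effect rate.
- Section 3.2 names one between-group safety analysis: "Chi-square analysis will be used to compare groups with regard to demographics, blindness, and safety measures (categorical variables". A general sentence adds Bonferroni correction where appropriate, without saying whether safety is covered.
- Section 3.3 gives the safety hypothesis: "The Parietal, Frontal, and Sham groups will not differ in blindness or safety measures".
- Section 4 describes the ambition: "This study will constitute the first attempt to prove the safety and feasibility of multiple (e.g., 10 sessions) and consecutive sessions of tRNS".

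**The concern.** The hypothesis is that there is no difference, but the test can only give evidence that there is one. Failing to reject equality is not evidence of equality, and it becomes more likely as fewer children are tested. With no margin, acceptable rate or interval criterion stated, the chi-square result is the only between-group yardstick the article offers for its first aim.

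The stake is the published safety statement. Section 2.7 acknowledges that safety data on tRNS are sparse, and section 4 presents the results as a step toward clinical translation. An excess of a less common side effect at one or both stimulation sites could be reported as no difference between groups and then cited as evidence of safety in children.

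The mismatch lies in what the article itself fixes (hypothesis, test and intended claim). It does not depend on how an analysis plan would code or tabulate the ratings.

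**Working it through.** **The plan's own figure.** Section 2.6 uses f = 0.15, "α value = 0.05 (i.e., probability of false positives of 5"%), and "β = 0.80 (i.e., at least 80% power"), with 3 groups and 4 measurements. For the within-between interaction, with assumed correlation 0.5 and sphericity (the usual software defaults):

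- λ = f² × N × m / (1 − ρ) = 0.0225 × 78 × 4 / 0.5 = 14.04
- df = (3 − 1)(4 − 1) = 6 and (78 − 3)(4 − 1) = 225
- Power = 0.801; at N = 75 it is 0.782

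So 78 reproduces, and 78 × 1.30 = 101.4 rounds up to 102, or 34 per arm. This calculation concerns efficacy only.

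**Inputs for the safety test**

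- n = 34 per arm (section 2.6). Because ratings are taken after every session, children lost later still contribute. The 26 evaluable per arm is a sensitivity case.
- Alpha = 0.05. This is stated for efficacy and assumed here for safety.
- One binary outcome per child (assumed).
- Sham rate: not given, so varied from 5% to 40%.
- Alternatives: the rate doubled or tripled in both active arms.

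**Formula.** With a, b and c the event counts in the three arms and p̄ = (a + b + c)/(3n), the Pearson statistic is X² = [(a − np̄)² + (b − np̄)² + (c − np̄)²] / [np̄(1 − p̄)]. Equality is rejected when X² > 5.99 (2 df). The chance of missing the increase is one minus the summed product of the three binomial probabilities over all (a, b, c) that reject, computed by full enumeration.

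**Chance of missing the increase, both active arms raised**

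| Sham rate | Doubling, n = 34 | Tripling, n = 34 | Doubling, n = 26 | Tripling, n = 26 |
|---|---|---|---|---|
| 5% | 91% | 77% | 94% | 85% |
| 10% | 81% | 46% | 87% | 59% |
| 15% | 70% | 19% | 77% | 31% |
| 20% | 57% | 4% | 66% | 11% |
| 30% | 26% | – | 39% | – |
| 40% | 4% | – | 10% | – |

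If only one active arm is raised from 10%, the misses at 34 per arm are 78% for a doubling and 38% for a tripling. For 80% power at a 10% sham rate, about 201 per arm would be needed for a doubling and 65 for a tripling (noncentral chi-square, both active arms raised).

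**What estimation can deliver.** With zero events in n children, the one-sided 95% upper limit is 1 − 0.05^(1/n). This is 1 − 0.05^(1/68) = 4.3% for both active arms together and 1 − 0.05^(1/34) = 8.4% for one arm. For 20% in one active arm against 10% in sham, the 95% half-width of the risk difference is 1.96 × √(0.2 × 0.8/34 + 0.1 × 0.9/34) = 0.168, about 17 percentage points.

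**The case against.** **No decision rule is written.** Section 3.3 lists expectations, section 3.2 says only that groups will be compared, and section 4 speaks of an attempt. A reader might infer that p > 0.05 will be declared proof of safety. No sentence says so, and that reading should not be attributed to the plan. What stands is that no other between-group criterion is offered.

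**The test is not weak everywhere.** A reader might infer that it misses a doubling or tripling about half to four-fifths of the time. That holds only near a 10% sham rate, which the article does not give. Section 2.5.6 lists symptoms such as tingling, itching and sleepiness. If these are common in sham, the test performs well: a tripling from 20%, or a doubling from 40%, is missed about 4% of the time.

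**A Bonferroni penalty on safety is not established.** The correction applies only where appropriate, and the symptom list is illustrative, so no fixed number of tests follows from it.

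**The safety aim is not beyond rescue.** Graded reports after every session, adverse effects registered throughout (section 2.7) and continuous supervision (section 2.8) can support a descriptive safety statement. The limitation belongs to the test, not to the data.

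**Interval methods are often left to an analysis plan.** That is true, and their absence alone would be no finding. The hypothesis, the test and the claim of proof are, however, all fixed in this article, and they do not fit together.

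**Conclusion.** The point holds in a bounded form. A hypothesis of no difference in safety measures, examined by a chi-square difference test in a sample sized for efficacy, cannot support a safety conclusion for uncommon effects. At sham rates of 5% to 10% with 34 per arm, a doubling is missed 81% to 91% of the time and a tripling 46% to 77%. At 20% a doubling is still missed 57% of the time. For common effects the weakness largely disappears.

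These figures rest on assumed sham rates, one binary outcome per child, alpha 0.05 and an increase in both active arms. The primary efficacy analysis is unaffected. The change should be made, because safety is the first listed aim and the remedy uses data already planned.

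**What to change.** In sections 3.2 and 3.3, base the safety conclusion on estimation:

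- For each active arm and for both pooled (68 v 34 sham), report the proportion of children with at least one moderate or severe side effect, with an exact 95% confidence interval.
- Report the active-minus-sham risk difference with a 95% confidence interval.
- State that chi-square p-values for safety are descriptive and carry no Bonferroni correction.

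In section 4, replace the language of proof with the rate the trial can exclude. For example, no events in 68 active children would exclude rates above 4.3%, and none in 34 would exclude rates above 8.4%. These are one-sided 95% limits and should be labelled as such.

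The cost is rewording and a more modest safety statement, since the intervals will be wide. No extra children, visits or data are needed.

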### 2.3. Design, Randomization, and Blinding

The study will use a between-subject, randomized, double-blind, and sham-controlled design.

The screen for clinical eligibility will be completed on Day 0 of the trial, before the stratified randomization. Randomization occurs immediately after a participant completes the screening assessment, ensuring concealment of allocation. Participants will be allocated randomly to the following conditions: (1) Frontal Group (active tRNS over bilateral dlPFCs + cognitive training); (2) Parietal Group (active tRNS over bilateral PPCs + cognitive training); and (3) Sham Group (Sham tRNS over bilateral dlPFCs/PPCs + cognitive training). An independent researcher will perform the stratified randomization. The stratified randomization will use the minimal sufficient balancing method to prevent imbalances in baseline and will be based on the participants’ demographics (e.g., age, IQ, gender) and MTq [70].

The investigators who assess the participants will be blinded to the allocation, as will the participants and their parents. An independent researcher will maintain the randomization information until the data collection is completed. An emergency code break envelope will be provided to the principal investigator and will only be opened in the case of an emergency, such as a serious adverse event that requires knowledge of the interventions to manage the participant’s condition.

A baseline assessment (see Figure 1) will be completed on Day 1 (T0), before the interventions are administered. Participants will undergo combined interventions for 10 days (5 consecutive days per week for 2 consecutive weeks: from Day 1 to Day 5 and from Day 8 to Day 12). To minimize the influence of intracircadian variations, participants will attend stimulation sessions each day at the same time. Participants will also complete an assessment at the end of the interventions (Day 12, T1), 1 week later (Day 19, T2), and 3 months later (Day 102, T3). At the last follow-up, after the assessment, participants will be asked to guess their stimulation condition by the principal investigator.

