### 2.4. Interventions

#### 2.4.1. Cognitive Training

Vektor Cognition Matters (https://cognitionmatters.org/, accessed on 5 October 2021) [34,71] is a challenging open-source and age-based training software program that is designed to support and improve the learning of math in children and adolescents. Vektor consists of several domain-specific (numerical abilities) and domain-general tasks (working memory, mental rotation, and logical reasoning) that are automatically and equally alternated for 20 min. As an adaptive training program, it is calibrated to each individual’s performance.

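### Hypothesis 4 predicts change–change correlations in the two active groups with no comparison against Sham, so shared cognitive training alone could confirm a link that the article ties to tRNS

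*Protocol article*

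**What the plan says.** Section 3.3 lists four expectations. The first compares all three groups, and the second and third are set against Sham. The fourth has no comparator: "In the Parietal and Frontal Groups, arithmetic changes will correlate strongly and positively with changes in neuropsychological and spectral power EEG measures", with psychological measures added for T3.

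The method in section 3.2 is "Pearson’s correlation will be used to determine whether and the extent to which arithmetic improvements are related to changes in neuropsychological measures", and likewise to changes in psychological measures and EEG band power, at T1, T2 and T3 from T0. No group term, interaction or comparison of coefficients is given. The section does not say whether the correlations are run by arm, in the active arms together or in all children.

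The purpose is worded around tRNS. Objective 3 in section 1.3 is "Testing whether and the extent to which arithmetic improvements after tRNS are related to neuropsychological changes", and objective 4 asks the same of EEG changes following tRNS. Section 2.5.5 calls EEG a biomarker of what tRNS induces, and the Discussion calls it a marker for treatment responders.

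The control arm is "Sham Group (Sham tRNS over bilateral dlPFCs/PPCs + cognitive training" (section 2.3). Besides numerical tasks, the training contains "domain-general tasks (working memory, mental rotation, and logical reasoning" (section 2.4.1). The neuropsychological outcomes in section 2.5.2 are N-back, a working memory task, and Geometric Puzzle, which measures mental rotation.

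**The concern.** The training exercises arithmetic together with the very skills that the neuropsychological outcomes measure, and every arm receives it. Children who respond well to training may gain on both kinds of test whether or not the stimulator is on. A positive correlation inside an active arm is therefore expected under two explanations: training alone, or a link specific to tRNS. Only a comparison with Sham can separate them, and neither section 3.2 nor section 3.3 provides one.

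At stake is the mechanistic reading. The trial could present a neuropsychological or EEG change as a correlate or responder marker of tRNS when the same association holds under sham.

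The group comparison of means does not fill the gap. The mixed model covers "continuous variables: arithmetic, neuropsychological, and psychological measures" as secondary outcomes, but a difference in means does not show that the association differs. EEG power is not named in that list.

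**Working it through.** **1. Inputs.** From section 2.6: 78 required (26 per group), alpha 0.05, 30% dropout in the follow-ups, 102 recruited (34 per group). Completers per arm: 102 × 0.7 / 3 = 23.8, about 24. The documents give no correlation, so true r = 0.3, 0.4 and 0.5, equal in all arms, are assumptions.

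**2. The plan's own figure.** For the group-by-time interaction, λ = f²·N·m/(1 − ρ) = 0.15² × 78 × 4 / 0.5 = 14.04, with 6 and 225 degrees of freedom, gives power 0.801. So 78 reproduces if ρ = 0.5 and sphericity are assumed (neither is stated). It sizes the mean comparison, and the present point does not depend on it.

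**3. Smallest significant correlation.** r = t/√(n − 2 + t²). At n = 24, t = 2.074, so r = 2.074/√(22 + 4.30) = 0.404. At n = 34, r = 0.339.

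**4. Chance of significance in one active arm, n = 24.** Fisher z: power = Φ(atanh(r)·√(n − 3) − 1.960), with √21 = 4.583.
- r = 0.3: Φ(1.418 − 1.960) = 0.294
- r = 0.4: Φ(1.941 − 1.960) = 0.493
- r = 0.5: Φ(2.517 − 1.960) = 0.711

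**5. How often hypothesis 4 would appear supported when the association is identical in Sham.** The answer depends on how the hypothesis is read:
- At least one active arm significant, 1 − (1 − p)²: 0.502, 0.743, 0.917
- Both active arms significant, p²: 0.086, 0.243, 0.506
- Active arms pooled (n = 48, √45 = 6.708), Φ(atanh(r) × 6.708 − 1.960): 0.546, 0.811, 0.958

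Under equal correlations, a direct Fisher z test of one active arm against Sham rejects in about 5% of trials (simulation at 26 per arm: 5.2% at r = 0.3, 5.1% at r = 0.5).

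**6. Sensitivity of the at-least-one figure.**
- 34 per arm, if nobody is lost by T1: p = 0.406, 0.655, 0.864, giving 65%, 88%, 98%
- Bonferroni over 4 tests (assumed family, z = 2.498), n = 24: p = 0.140, 0.289, 0.508, giving 26%, 49%, 76%
- Bonferroni over 12 tests (assumed: four bands × three times, z = 2.865), n = 24: p = 0.074, 0.178, 0.364, giving 14%, 32%, 60%

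**7. Power of the missing contrast.** The standard error of a difference of two Fisher z values at 24 v 24 is √(2/21) = 0.309. For r = 0.5 v 0: Φ(0.549/0.309 − 1.960) = Φ(−0.18) = 0.43. For 0.5 v 0.2: about 0.20. With 34 v 34, 0.5 v 0 gives 0.58.

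**8. Common association.** In all 71 or so children, adjusted for group, the critical |r| is about 0.24, and power is about 71% at r = 0.3 and 93% at r = 0.4.

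**The case against.** The article is condensed, and an unspecified correlation model is close to what a separate analysis plan would settle. That has weight for details such as the model and the test family. It does not remove the point, because the article fixes both the hypothesis and the tool, and the two together do not answer objectives 3 and 4.

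The outcomes are secondary, section 2.5.5 calls the EEG use exploratory, and efficacy is compared with Sham by mixed model. All of this stands and limits the consequence. The neuropsychological and psychological correlations carry no exploratory label, however.

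Several stronger readings are tempting but are not supported:
- A reader might infer that the plan splits the data by arm and so wastes information. Section 3.2 does not say so; the restriction to active groups comes from the list of expected results. Pooling all arms without a group term would not isolate a tRNS-specific link either.
- A reader might infer that significance in an active arm with none in Sham will be offered as proof. No section announces that inference.
- A reader might infer that the correlation will appear in Sham. That is plausible for working memory and mental rotation, but not shown. For resting EEG, anxiety or parental stress the training does not target the measure directly.
- Objective 5 might be read as a tRNS claim too. It names neither tRNS nor any arm.

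**Conclusion.** The point holds as a limit on interpretation. Followed as written, hypothesis 4 can be confirmed by training alone, so its confirmation would not support a tRNS-specific association. The case is strongest for the neuropsychological measures and weaker for EEG and psychological measures.

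Under an equal assumed r of 0.3 to 0.5, 24 per arm and unadjusted alpha, at least one active arm is significant in about 50% to 92% of trials. The range falls to 14% to 60% with a 12-test Bonferroni family, and rises to 65% to 98% with 34 per arm and no adjustment. These figures illustrate the problem and are not predictions, since the true correlations, the test family and the arms analysed are all unstated. A correction for multiplicity changes the rates but does not supply the missing contrast.

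A reader might go further and doubt the efficacy result. The documents do not support that: the primary outcome and the mixed-model comparisons with Sham are untouched.

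**What to change.** In section 3.2, for each marker fit one regression on all three arms: arithmetic change on marker change, Group, and Group × marker change, adjusted for both baselines.
- Report the common slope as the association.
- Report each active-minus-Sham difference in slope with a confidence interval, as the only basis for any tRNS-specific statement.
- Show Pearson r by arm, Sham included, as description.

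Reword item 4 of section 3.3 to match, and make the biomarker and responder-marker wording in section 2.5.5 and the Discussion conditional on that contrast.

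The cost is wording only: no new data, visits or children. The drawback is low power. Using the Fisher z figure as a guide to the slope contrast, it is about 43% for r = 0.5 v 0 at 24 per arm. The contrast should therefore be presented as an estimate, a non-significant difference should not be read as equality, and claims about a tRNS mechanism will be more modest.
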